### Assessments

All patients in the care of the CReSM are evaluated by neurologists with the EDSS (Expanded Disability Status Scale). The psychological assessment will be performed with the same timing and tools: at baseline (T0), after treatment (T1) and 6 months after the end of the group intervention (T2). The psychological assessment of the patients entering the study will be performed by trained Clinical Psychologists with more than 3 years of clinical practice in the liaison setting. The psychological assessment will be independent and blind to treatment, and will encompass the administration of the following clinical interview and self-report questionnaires.Structured Clinical Interview-DSM-IV (SCID-IV) [31]: is a well-validated, semi-structured interview, which covers the Diagnostic and Statistical Manual of Mental Disorders, 4th Edition (DSM-IV) criteria for adult psychopathology.Beck Depression Inventory-II (BDI) [32]: it is a 21-item self-report instrument that assesses the presence and severity of symptoms consistent with the criteria of the DSM-IV. Each item is scored on a 4 point scale ranging from 0 to 3 with total scores ranging from 0 to 63, where higher scores are indicative of higher levels of depression. The Consensus Group for depression in MS [12] and the American Academy of Neurology [13] stated that the best approach to screening for depression in general MS populations is to use the BDI-II, with a cut-off score of 13.Functional Assessment of Multiple Sclerosis (FAMS) [33]: it is a self-report scale designed to assess six primary aspects of QOL of patients with MS: Mobility, Symptoms, Emotional Well-Being, General Contentment Thinking and Fatigue, and Family/Social Well-Being.Beck Anxiety Inventory (BAI) [34]: is a 21-item self-report measure that assesses cognitive, somatic, and affective anxiety symptom severity. Each item is rated on a Likert scale from 0 to 3, and the total BAI score can range from 0 to 63, where higher scores are indicative of higher levels of anxiety.Fatigue Severity Scale (FSS) [35]: is a self-administered questionnaire with 9 items investigating the severity of fatigue in different situations during the past week. This items are designed to differentiate fatigue from clinical depression.Inventory of Interpersonal Problems (IIP) [36]: is a self-report instrument that identifies a person’s most salient interpersonal difficulties. The IIP contains 64 statements describing common interpersonal problems.Brief Illness Perception Questionnaire (IPQ-Brief) [37]. It is a nine item self-report measure that is used to assess the major components of illness perceptions. The questionnaire assesses each dimension using a single-item scale from 0 to 10.Perceived Stress Scale (PSS) [38]. It is a 10-item measure of the degree to which situations in one’s life are appraised as stressful. The items refer to people’s subjective appraisals of events.Post Traumatic Growth Inventory (PTGI) [39], a 21-item instrument for assessing positive outcomes in people who have experienced traumatic events. It measures five domains or factors: relating to others, new possibilities, personal strength, spiritual change, and a deeper appreciation of life.Five Facet Mindfulness Questionnaire (FFMQ) [40], a 39-item self-report questionnaire measuring five unique facets associated with the overarching construct of mindfulness disposition. The facets included are observing, describing, acting with awareness, nonjudgment, and nonreactivity.A clinical diary of the homework practice: it is a clinical diary regarding frequency and duration of homework assigned in the group sessions, that patients are asked to fill out every time they spent time on homework practice.

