#### Outcome measures and statistical analysis

Primary outcome measures will be: 1) the improvements of BDI-II score from T0 to T2; 2) the proportion of participants at T2 that do not have a BDI-II score greater than 13.

Secondary outcome measures will be the comparison of the scores of FAMS, BAI, FSS, IIP, IPQ-Brief, PSS, PTGI and FFMQ of the two groups at T0, T1 and T2. Another secondary outcome aim will be the reduction of psychological symptoms (BDI-II, BAI, IIP, PSS, PTGI) and a reduction in QoL (WHOQoL-Brief) in caregivers of patients with MS.

The efficacy of MBI will be evaluated by comparing the results to different instruments administered to patients before participating at MBI (T0), after MBI (T1) and at the 6-month follow-up (T2) and by comparing these results with those of patients who were included in the active control group. Intention to treat analyses will be used.

A longitudinal (within subjects) and cross sectional (between subjects) evaluation of our outcome measures will be performed through a repeated measures multivariate analysis of covariance (ANCOVA) using the SPSS GLM procedure. The pre-treatment value will be the covariate, and the treatment condition will be the inter-subjects factor. The intra-subject factor will be a time condition, relating to changes from post-treatment to 6-month follow-up.

The proportion of participants at T1 and T2 no longer meeting the BDI-II cut-off criteria for depression will be evaluated through the Chi square test.

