#### Power calculation

The sample size calculation is based on the primary outcomes for patients with MS.

Statistical power calculation was based on previous studies [28, 48]: assuming power =0.80 and 0.05 significance, a minimal sample size of 44 patients/group will be required, based on an effect size of 0.54.

To obtain the 88 patients needed for the study, it is expected to do the screening of at least 600 patients. On the basis of the information that is available on the prevalence of depression in MS patients, on the average 25 % in previous studies, this number should guarantee there will be at least 150 participants. The number of refusals and treatment interruptions is estimated at not above 40 % which leads to about 90 cases.

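### Run as written, the named SPSS GLM repeated-measures model analyses only patients with complete T0, T1 and T2 records, which does not deliver the promised intention-to-treat analysis

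*Protocol article*

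**What the plan says.** All of this stands in the Protocol article, mostly under Outcome measures and statistical analysis.

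- **Principle:** "Intention to treat analyses will be used".
- **Model:** the evaluation "will be performed through a repeated measures multivariate analysis of covariance (ANCOVA) using the SPSS GLM procedure".
- **Covariate and factor:** "The pre-treatment value will be the covariate, and the treatment condition will be the inter-subjects factor".
- **Within-subject levels:** "The intra-subject factor will be a time condition, relating to changes from post-treatment to 6-month follow-up", that is, T1 and T2.
- **Primary outcomes:** "1) the improvements of BDI-II score from T0 to T2; 2) the proportion of participants at T2 that do not have a BDI-II score greater"; the cut-off is 13. Both are read at T2. The proportion is compared by chi-square test.
- **Visits (Assessments):** "at baseline (T0), after treatment (T1) and 6 months after the end of the group intervention (T2").
- **Sample size (Power calculation):** "assuming power =0.80 and 0.05 significance, a minimal sample size of 44 patients/group will be required, based on an effect size of 0.54". The Abstract gives 88 randomised, which is exactly 2 × 44.
- **Attrition (Power calculation):** "The number of refusals and treatment interruptions is estimated at not above" 40%, applied to the 150 patients expected to be depressed and leaving about 90.

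The article states no imputation step, likelihood-based model or sensitivity analysis for missing values.

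**The concern.** In SPSS GLM repeated measures, each visit is a separate dependent variable and each patient is one row. A row with any missing dependent variable or covariate is excluded. Two kinds of patient are then lost although they hold useful data: those seen at T2 but not at T1, whose primary endpoint is known, and those seen at T1 but not at T2, whose T1 score predicts the missing value.

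The analysis set becomes the patients who attended every assessment. If the arms lose different patients for reasons related to response, the comparison is no longer protected by randomisation. Differential loss is plausible here. The MBI arm has an additional 7-hour session that the control arm lacks, and its 45-minute daily homework is described as required, while control homework is described as encouraged. T2 comes six months after the groups end, when some missing assessments are to be expected.

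This goes beyond a detail left to another document. The article fixes a procedure for the first primary outcome that, used as described, falls short of the principle stated just before it.

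**Working it through.** **1. Which records enter the model.** Inputs are the covariate (T0) and the within-subject levels (T1, T2), from Outcome measures and statistical analysis.

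| T0 | T1 | T2 | Primary endpoint observed? | In GLM? | Used by a mixed model? |
|---|---|---|---|---|---|
| yes | yes | yes | yes | yes | yes |
| yes | no | yes | yes | no | yes |
| yes | yes | no | no | no | yes, through T1 |
| yes | no | no | no | no | only if T0 is modelled as a response |

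Because both follow-ups are needed, losses compound. If 10% were missing independently at each visit (an assumption), 0.9 × 0.9 = 81% would be complete.

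**2. The plan's own sample size.** For a two-group comparison with standardised effect 0.54, n per group = 2(z_α + z_β)²/0.54². At one-sided 0.05 and power 0.80, the normal formula gives 43 and the t-test 43.1, rounded up to 44, which is the stated figure. Two-sided, it gives 54 (t-test 55). Sidedness is not stated. A two-sided baseline-adjusted comparison with a correlation of about 0.43 also gives 44: 53.8 × (1 − 0.43²) = 43.9. The recruitment arithmetic holds: 600 × 0.25 = 150 and 150 × 0.60 = 90. The 88 randomised leave no margin over 2 × 44 for deleted records.

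**3. Possible bias.** The article gives no rate of missing assessments, so every input here is an assumption:
- no true effect;
- correlations T0–T1 0.5, T0–T2 0.4, T1–T2 0.6;
- control loss at T2 random;
- MBI loss at T2 logistic on the T1 score, with a log-odds slope of 0.25 to 1.5 per SD (worse scores more likely to leave).

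The complete-case ANCOVA was fitted to large simulated samples (one million per arm). Entries are the spurious MBI benefit in SD, at T2 / for the T1–T2 average.

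| Slope per SD | 15% control, 22% MBI | 10% control, 28% MBI |
|---|---|---|
| 0.25 | 0.02 / 0.03 | 0.03 / 0.04 |
| 0.5 | 0.04 / 0.06 | 0.05 / 0.08 |
| 1.0 | 0.08 / 0.11 | 0.10 / 0.14 |
| 1.5 | 0.10 / 0.15 | 0.13 / 0.18 |

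The range is 0.02 to 0.18 SD. Against 0.54 that is 0.02/0.54 = 4% to 0.18/0.54 = 33%. A likelihood-type estimate of the T2 effect that uses the observed T1 values was within 0.002 SD of zero in every row. That follows from the assumption that dropout depends only on the T1 score.

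**4. Precision.** The planned model adjusts for T0. With correlation r between T0 and T2, the effective standardised effect is 0.54/√(1 − r²). At r = 0.4 this is 0.54/√0.84 = 0.589. Two-sided power with 44 per group is then 78%, and with 15% lost (37.4 per group) it is 71%. The unadjusted two-sided t-test would go from 71% to 63%, but that is not the planned analysis. A mixed model recovers only part of the loss, because a patient without T2 still has no T2 value.

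**The case against.** The strongest reply is that GLM works on whatever data set it is given. If missing values were multiply imputed first, the intention-to-treat promise and the GLM procedure would both be honoured, and a full analysis plan might say so. That stands. A reader might infer that the two statements are irreconcilable, and the article does not support that. What remains is that the article names the procedure and states no step before it, so followed literally it yields complete cases.

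A reader might also take the 40% under Power calculation as the expected dropout. It is not. It combines refusals with treatment interruptions among patients found eligible, and stopping treatment is not the same as missing an assessment. A patient who leaves the sessions but completes T1 and T2 stays in the model in the assigned arm. The Background also cites low attrition for mindfulness programmes, so the loss may prove small.

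Finally, a reader might infer that the deletion favours MBI. The table in the working has that sign because poor responders were assumed to leave the MBI arm. If good responders left instead, the sign would reverse. The control arm shares the weekly format and also has homework, so unequal loss is plausible but not shown.

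**Conclusion.** The point holds in a limited form. As written, the analysis of the first primary outcome is restricted to patients with complete T0, T1 and T2 scores, and excludes some whose T2 endpoint was observed. This falls short of the stated intention-to-treat principle and is open to attrition bias if loss differs by arm and depends on response.

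That conclusion rests on how the named procedure treats missing values and on the absence of any stated imputation. The size and direction of bias cannot be derived from the article. The 0.02 to 0.18 SD is conditional on the assumed loss rates, correlations and dropout slopes, and on MBI dropout depending on the T1 score. The chi-square comparison at T2 has a related gap, since nothing says how patients without a T2 score are counted.

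**What to change.** Replace the GLM procedure by a linear mixed model for repeated measures (for example SPSS MIXED):

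- include all randomised patients in the arm to which they were allocated, with every observed T1 and T2 value;
- include terms for T0 score, treatment, time and treatment × time;
- name the treatment contrast at T2 as the primary result.

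Patients with neither T1 nor T2 add nothing to this model unless T0 is entered as a response with equal arm means. Multiple imputation before GLM is an acceptable alternative and keeps the named procedure.

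Analyse the proportion with BDI-II not above 13 at T2 in all randomised patients, using multiple imputation. Add a sensitivity analysis for data missing not at random, because both the mixed model and standard imputation assume missing at random.

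The cost is a few sentences in the analysis section and slightly more analysis work, with the same software, the same visits and no new data. The choice should be fixed before outcome data are seen.

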The aim of the current paper is to describe our research design. Our primary objective is to evaluate the efficacy of MBI on depressive symptoms of MS patients, compared to an active control intervention, and to assess whether these expected benefits can be maintained at the 6-month follow-up. Secondary aims of the study are: to assess whether after the Mindfulness Based Intervention there is an improvement in QoL, anxiety, fatigue and perceived stress levels; to evaluate the efficacy of the intervention on the perception of the illness and whether participating in MBI also improve interpersonal relationships; to evaluate the efficacy of MBI on depression, QoL and related symptoms in caregivers.

We hypothesize that MBI intervention will lead to a reduction of depressive symptoms, and its associated symptoms both at a physical and psychological levels, compared to an active control group.

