### Participants

The subjects of the study will be 88 patients with MS and depressive symptoms that will be pre-screened from a catchment group of about 600 patients using the Beck Depression Inventory-II (BDI-II). Those who have a score on BDI-II greater than 13 (considered the best approach to screening for depression in MS patients following the Goldman Consensus Group) [12] will be assessed with the other psychological measures.

Inclusion criteria are as follows:—definite diagnosis of MS (Mc Donald Criteria) [30] evaluated by a neurologist of the CReSM Unit at least 6 months prior the beginning of the study;—relapsing-remitting and secondary progressive disease;—age of 18–65 years;—clinically inactive phase of the disease;—an Expanded Disability Status Scale (EDSS) score lower than 6.5;—fluent Italian speaker;—legal capacity to consent to the treatment;—willingness to abstain from or to suspend all concomitant psychological treatment;—suspension of all psychotropic medications at least 1 month before the treatment or maintenance at baseline level throughout the study.

Exclusion criteria are as follows:—current severe Major Depressive Disorder (as assessed by Structured Clinical Interview-DSM-IV (SCID);—severe suicidality, including ideation, plan, and intent;—current serious psychological and psychiatric disorders, including psychotic disorders, bipolar disorders, active substance abuse (as assessed by the SCID);—presence of overt dementia;—corticosteroid treatment during the previous 30 days;—other serious medical disorders in addition to MS;—current pregnancy.

The research protocol will be proposed to patients who will meet the inclusion criteria, with an explanation of the aims of the study and declaring the possibility that they are assigned by random allocation to MBI group or to control group. Patients who will give informed consent will be included in the study.

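### With the baseline score entered as recorded, the SPSS GLM time test for BDI-II describes the T1-to-T2 change at a baseline score of 0, far outside the screened sample; centring the covariate repairs it at no cost

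*Protocol article*

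**What the plan says.** All of the following is in the Protocol article.

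- **Model and software** (Outcome measures and statistical analysis): a "repeated measures multivariate analysis of covariance (ANCOVA) using the SPSS GLM procedure".
- **Covariate and between-subject factor** (same section): "The pre-treatment value will be the covariate, and the treatment condition will be the inter-subjects factor". Nothing is said about centring the covariate or about the baseline value at which time effects are tested.
- **Within-subject factor** (same section): "The intra-subject factor will be a time condition, relating to changes from post-treatment to 6-month follow-up". Time therefore has two levels, T1 and T2.
- **Entry screen** (Participants): "Those who have a score on BDI-II greater than 13" go on to the remaining psychological assessment. The Assessments section gives the BDI-II "total scores ranging from 0 to 63".
- **Objective** (end of Background): besides efficacy against the active control, the primary objective is "to assess whether these expected benefits can be maintained at the 6-month follow-up".
- **First primary outcome** (Outcome measures and statistical analysis): "the improvements of BDI-II score from T0 to T2".

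**The concern.** With two time points, the within-subject part of this model is an ordinary regression of D = T2 − T1 on an intercept, treatment (effect-coded) and T0. The time main effect is the test of the intercept. An intercept is the fitted value where the covariate equals zero, so with T0 as recorded the test concerns the mean T1-to-T2 change, averaged over the two arms, at T0 = 0. The screen admits scores of 14 or more, so the model is extrapolated at least 14 points below any screening score. A repeat T0 measurement could fall somewhat under 14, but 0 remains remote.

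The section describes the time factor as relating to change between end of treatment and 6 months. For the enrolled patients that description is correct only if T0 is centred or the change is tested at mean T0. Otherwise a reader may take a non-significant time row as stability when the test had little chance of detecting a change, or a significant one as change when the patients did not change on average.

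**Working it through.** **No plan figure to reproduce.** The article gives no power or expected value for the time test. Its 44 per group belongs to the between-arm comparison and is used here only for the number of patients.

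**Inputs from the Protocol article.** 88 patients, 44 per arm (Power calculation); screen above 13 (Participants); two time levels and T0 as covariate (Outcome measures and statistical analysis). The 0.05 level is from "assuming power =0.80 and 0.05 significance" and is applied two-sided, as the F test does.

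**Assumed inputs, not in the documents.** T0 mean 22, SD 7; SD at T1 and T2 8.5; T1–T2 correlation 0.70; T0–T1 correlation 0.55. The T0–T2 correlation is 0.55 (equal slopes) or falls to 0.45 or 0.40.

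**Step 1: standard error.** Relative to the change at mean T0, the standard error at T0 = 0 is multiplied by √(1 + (mean/SD)²) = √(1 + (22/7)²) = 3.30. For assumed means of 18 to 24 and SDs of 4 to 8 the multiplier runs from 2.5 to 6.1.

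**Step 2: equal slopes, true 2-point change.**
- Var(D) = 2 × 8.5² × (1 − 0.70) = 43.35, so SD(D) = 6.58.
- SE at mean T0 = 6.58/√88 = 0.70. Ratio 2/0.70 = 2.85, power about 80%.
- SE at T0 = 0 is 0.702 × 3.30 = 2.31. Ratio 2/2.31 = 0.86, power about 13 to 14%.
- For 3 points the same steps give about 25% against 99%.

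**Step 3: no mean change, baseline predicts T2 less well.** The slope of D on T0 is (r02 − 0.55) × 8.5/7, and the tested quantity is −slope × 22.

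| T0–T2 correlation | Slope of D | Value at T0 = 0 | SE at T0 = 0 | Rejects, T0 as recorded | Rejects, centred |
|---|---|---|---|---|---|
| 0.45 | −0.121 | 2.67 | 2.30 | about 21% | 5% |
| 0.40 | −0.182 | 4.01 | 2.27 | about 41% | 5% |

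Simulations of 5,000 and 6,000 trials agree: 13 to 14% against 80% in step 2; 20% and 39 to 41% against 5 to 6% in step 3.

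**Step 4: a true change together with a falling slope.** The slope term now adds to or subtracts from the change. At a T0–T2 correlation of 0.45, a 2-point worsening gives (2 + 2.67)/2.30 = 2.03, and rejection in about 51 to 52%. A 2-point improvement gives (−2 + 2.67)/2.30 = 0.29, and rejection in about 6%. Centred power is about 81% in both cases.

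**Step 5: other assumptions.** With T0 mean/SD of 20/5 or 22/7, residual SD 6 and residual correlation 0.5, 4,000 simulated trials gave power for 2 points of 12 to 15% against 86 to 88% centred (equal slopes). With no mean change, T0 slopes falling from 0.6 to 0.5 gave 11 to 17% rejection, and from 0.7 to 0.4 gave 60 to 84%; centred, about 5 to 6%.

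**Step 6: what does not move.** The time-by-treatment p-values were identical with T0 as recorded and centred (differences near 10⁻¹⁴). In one generated data set the between-arm effect was −2.831 (SE 1.109) both ways. The chi-square test does not use T0.

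**The case against.** **The article never says uncentred.** This is true, and a full analysis plan could centre T0 without contradicting the text; covariate scaling is often left to such a plan. What stands against it is that the article names procedure, covariate and time factor, and attaches a meaning to that factor. Followed as written, the output does not carry that meaning. The point is therefore conditional on T0 being entered as recorded.

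**The time row is not named as the test of maintenance.** This also stands. A reader might infer, from the maintenance objective and the description of the time factor, that this row decides whether benefit lasts. The text defines a factor, not a decision rule, and says efficacy is judged by comparison with the control patients. That question belongs to the treatment and time-by-treatment terms, which are sound. Even when centred, the time row pools both arms and does not describe MBI alone.

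**The harm has no fixed direction.** A reader might infer that a real loss of benefit would usually come out non-significant. That holds with equal slopes, but with falling slopes a 2-point worsening is detected in roughly 51 to 74% of trials.

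**Other scales.** A reader might extend the same size of error to every secondary measure. The screen above 13 concerns the patients' BDI-II only. BAI and IPQ-Brief items start at 0, and caregivers face no threshold, so the size there depends on how far the T0 mean lies from zero relative to its SD.

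**Conclusion.** The point holds for one test: the BDI-II time main effect, if T0 enters as recorded. That test is unreliable for the enrolled patients. Under an assumed T0 mean of 22 and SD of 7, it has about 13% power instead of 80% for a 2-point change with equal slopes, and about 20 to 40% false rejection instead of 5% when baseline predicts T2 less well than T1. These sizes rest on assumed means, SDs and correlations, and which error occurs depends on slopes that are not known. The extrapolation to T0 = 0 and the inflated standard error follow from the model itself.

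A reader might take the title outcome of change to 6 months to be at risk. It is not: the primary outcomes concern T0 to T2 and the proportion at or below the cut-off at T2, and the MBI-versus-control comparison is unchanged. This is a free improvement of minor to moderate weight.

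**What to change.** In Outcome measures and statistical analysis, add wording along these lines:

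- For each outcome, T0 is entered centred at its overall sample mean (both arms together). Alternatively, the T1-to-T2 change is tested at mean T0 through estimated marginal means.
- The T1-to-T2 change is reported per arm with a 95% confidence interval.
- The time-by-treatment term is the test of whether the difference between arms is maintained from T1 to T2.

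The cost is a few lines of text and one computed variable per outcome, or an estimated marginal means request. No patients, visits or data are added, and no other test in the plan changes.

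### The first primary outcome is BDI-II improvement from T0 to T2, but the specified repeated-measures ANCOVA does not name its T2 contrast as the primary test

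*Protocol article*

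**What the plan says.** All of the analysis text is in the Protocol article, section Outcome measures and statistical analysis.

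- **Outcome.** "Primary outcome measures will be: 1) the improvements of BDI-II score from T0 to T2". A second, binary primary outcome is "the proportion of participants at T2 that do not have a BDI-II score greater than 13".
- **Continuous analysis.** The evaluation "will be performed through a repeated measures multivariate analysis of covariance (ANCOVA) using the SPSS GLM procedure".
- **Covariate and treatment factor.** "The pre-treatment value will be the covariate, and the treatment condition will be the inter-subjects factor".
- **Time factor.** On the repeated measurements the article adds: "The intra-subject factor will be a time condition, relating to changes from post-treatment to 6-month follow-up". The Assessments section defines T1 as after treatment and T2 as 6 months after the group programme ends, so the time factor has two levels, T1 and T2.
- **Binary analysis.** "The proportion of participants at T1 and T2 no longer meeting the BDI-II cut-off criteria for depression will be evaluated through the Chi square test".

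The aims at the end of the Background set efficacy against the active control as the primary objective and add "to assess whether these expected benefits can be maintained at the 6-month follow-up". The general sentences on within-subject and between-subject evaluation name no contrast or time point that decides the primary outcome.

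**The concern.** A repeated-measures ANCOVA of this form produces two tests that involve treatment. The between-subject test compares the arms on the mean of T1 and T2. The treatment-by-time test asks whether the arm difference changes between T1 and T2. The primary outcome is about T2 alone.

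An analyst who follows the text has two candidate tests and no rule for choosing between them. If the average is taken as the primary test, a benefit seen mainly just after the course can count towards a 6-month outcome, and a benefit that develops late is diluted. The choice could also be made after the results are seen.

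**Working it through.** **1. The plan's own figure.** Power calculation: effect size 0.54, power 0.80, significance 0.05, 44 per group. For two independent means, one-sided 0.05 gives n = 2(1.645 + 0.842)²/0.54² = 42.4, so 43; the t-based value is 43.1, so 44. The stated figure is therefore reproduced one-sided. Two-sided, the same formula gives 2(1.960 + 0.842)²/0.54² = 53.8, so 54 (t-based 55). The article does not state sidedness. That is a separate matter; here 44 per group is taken as given and tests are two-sided.

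**2. What the model tests.** Let d1 and d2 be the baseline-adjusted arm differences at T1 and T2.
- Treatment main effect: (d1 + d2)/2
- Treatment by time: d2 − d1
- Primary outcome: d2

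With T0 as covariate, analysing the T2 score or the T0-to-T2 change gives the same treatment estimate, because subtracting T0 only shifts the coefficient of T0. In simulation the two differed by less than 1e-14. Also d2 = (d1 + d2)/2 + (d2 − d1)/2, so the stated model contains the T2 contrast.

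**3. Size.** Assumptions not in the documents: 0.54 is in SD units, data are complete, T0 has the same correlation r with T1 and T2, and T1 and T2 have correlation q. Put v = 1 − r² and c = q − r². With 44 per group:
- SE(average) = √[(2/44)(v + c)/2]
- SE(T2) = √[(2/44)v]
- SE(treatment by time) = √[(2/44)·2(v − c)]
- Rejection rate = Φ(d/SE − 1.96) + Φ(−d/SE − 1.96)

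Example, r = 0.5 and q = 0.6: v = 0.75, c = 0.35, and the SEs are 0.158, 0.185 and 0.191. With d1 = 0.54 and d2 = 0, the average is 0.27 and 0.27/0.158 = 1.71, which gives 40%. Treatment by time is 0.54/0.191 = 2.83, which gives 81%. The T2 test stays at 5%.

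Rejection rates in %, as average / treatment by time / T2 contrast:

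| r, q | 0.54 then 0 | 0.54 then 0.20 | 0 then 0.54 | 0.54 at both |
|---|---|---|---|---|
| 0.3, 0.5 | 34 / 72 / 5 | 57 / 36 / 17 | 34 / 72 / 76 | 88 / 5 / 76 |
| 0.3, 0.7 | 31 / 91 / 5 | 51 / 54 / 17 | 31 / 91 / 76 | 83 / 5 / 76 |
| 0.5, 0.6 | 40 / 81 / 5 | 65 / 43 / 19 | 40 / 81 / 83 | 93 / 5 / 83 |
| 0.5, 0.8 | 35 / 98 / 5 | 58 / 71 / 19 | 35 / 98 / 83 | 88 / 5 / 83 |

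A simulation of 4,000 trials at r = 0.5, q = 0.6 agrees. Effect 0.54 then 0: 39 / 80 / 5. Effect 0 then 0.54: 38 / 80 / 83.

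**4. Sensitivity.** Over every combination of r from 0.3 to 0.6 and q from 0.5 to 0.8, the average in the complete-fade case runs from 29% (r = 0.3, q = 0.8: SE 0.192, 0.27/0.192 = 1.41) to 53% (r = 0.6, q = 0.5: SE 0.133, 0.27/0.133 = 2.03). The T2 contrast stays at 5% in that case. The size moves with the correlations; the direction does not.

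**The case against.** The strongest reply is that nothing in the article is a wrong test. It never says that the main effect decides the primary outcome, and the fitted model yields the T2 difference directly as the difference in estimated marginal means at T2. Naming the deciding contrast is often left to an analysis plan, which is not shown. Most of this stands: the fault is an unnamed contrast, and a reader who infers that the stated analysis cannot answer the primary question goes too far. What remains is that the article itself fixes the outcome, the model and the time factor, and the model's standard treatment terms do not match the outcome.

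A reader might also infer that a vanished benefit would pass unnoticed as success. The figures do not support that as the usual result. Under a complete fade or a late effect, treatment by time is significant in 72–98% of trials. With equal residual variances the average and the T1-to-T2 change are uncorrelated. At r = 0.5, q = 0.6, a significant average without a significant interaction therefore occurs in about 0.40 × 0.19 = 8% of trials. Protection is weaker for a partial fade (0.54 then 0.20): 0.65 × 0.57 = 37%.

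Two further readings fail. The 5% interaction rate under a constant effect is no defect, since maintained benefit is exactly the absence of change from T1 to T2. And the Background aim is not a conflicting definition of the primary outcome: efficacy with maintenance at 6 months is compatible with T0-to-T2 improvement.

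Finally, the second primary outcome has its own chi-square test at T2, so the 6-month question is not left without any matched test.

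**Conclusion.** The point holds as a mismatch between the first primary outcome and the treatment terms of the only continuous analysis specified. For the four correlation pairs tabulated:

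- **Effect gone by T2:** the average is significant in 31–40% of trials, against 5% for the T2 contrast.
- **Effect falling to 0.20:** 51–65% against 17–19%, with treatment by time significant in 36–71%.
- **Effect only at T2:** 31–40% against 76–83%.
- **Constant effect:** the average estimates the same quantity as the T2 contrast and has more power, so there is little harm.

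The mismatch matters only if the effect fades or emerges. The protocol leaves that open by asking whether benefits are maintained. The correlations and the effect patterns over time are assumptions; the documents give only the effect size of 0.54 and 44 per group. This should be fixed, because it settles what counts as success on a primary outcome, but it does not invalidate the planned model.

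**What to change.** In Outcome measures and statistical analysis, state that the primary continuous test is the baseline-adjusted between-arm difference in BDI-II at T2. Take it as the T2 contrast (estimated marginal means at T2) from the stated repeated-measures ANCOVA, or as an ANCOVA of T2 on T0, which gives the same estimate when the same patients are analysed. Report the estimate with its 95% confidence interval. Make the T1 contrast secondary and treatment by time supportive. The chi-square test at T2 stays for the second primary outcome. No mixed model is needed for this purpose.

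The change is to wording only; no visit or procedure is affected. The cost is power if the effect is constant over time: about 76–83% for the T2 contrast against 83–93% for the average, for the tabulated pairs. At two-sided 5% and 80% power, the T2 contrast needs n = 2(1 − r²)(1.960 + 0.842)²/0.54² per group: 41 at r = 0.5, 46 at r = 0.4 and 49 at r = 0.3. Whether 44 is enough therefore depends on the baseline correlation.
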